## Methods/design

### Study design

The study is a two-armed prospective randomised controlled trial in which approximately 400 male and female adolescents aged 12 to 17 years will be randomised in a 1:1 ratio to the intervention or a wait-listed control group using a computer-generated random number sequence. Participants in both groups will complete assessments at baseline and post-intervention.

### Study Aim

The aim of this study is to evaluate the effectiveness of a TPB-based sun safety intervention for Queensland adolescents on increasing positive attitudes, normative support, and self-efficacy, leading to increased sun protection intentions and behaviour.

### Study Sample

#### Sample Eligibility Criteria and Recruitment Procedures

Ethics approval was received from the Queensland University of Technology Human Research Ethics Committee (approval number 1100000768). Eligibility criteria will include male and female students aged 12 to 17 years from public and private secondary schools across metropolitan and regional areas of Queensland, Australia.

A convenience sample of schools will be recruited using a maximum variation sampling method to ensure participating schools range in social-demographic status and geographical location. Schools will be approached to participate by the study team using an information package by phone, email and face-to-face discussions. The information package will include a letter to the school principal, background information about the study, questionnaire items, and the participant intervention workbook. Consenting schools will be requested to identify teachers (and their students) that will be accessible to the research team. Active consent will be obtained from both the student participating and their legal guardian. Baseline data will be collected from consenting students by the study team at a time and day specified by the school principal.

#### Sample size

A total of 400 participants (200/group) is aimed to be recruited. Based on our previous research in the area [28], it is anticipated that there will be approximately 35% attrition over 4 weeks of follow-up for reasons such as school absence or failure to complete follow-up questionnaires. A total sample of approximately 260 (400-140) completing participants (130/group) is required to detect a medium effect in sun safety behaviour. This sample size was determined by power analysis using the G*Power program [29,30]. Significance level (alpha) was established at 0.05 to avoid a Type 1 error, power (1-beta) was set at 95% to avoid a Type II error, and effect size was determined at .25. Therefore, for a 95% chance of detecting as significant a 4 week difference in sun safe behaviour, approximately 130 participants in each group are needed to complete the study.

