#### Intervention

The intervention will focus on: (i) encouraging supportive sun protective attitudes and beliefs, (ii) fostering perceptions of normative support for sun protection behaviour, and (iii) increasing perceptions of control/self-efficacy over using sun protection. Intervention sessions will be facilitated by trained persons from the Cancer Council Queensland and Queensland University of Technology. Facilitators and Queensland University of Technology research staff will be authorised to deliver the intervention with secondary school students during school hours, and all study staff directly involved with the participants and the running of the intervention will be approved to work with minors (have a current Positive Notice Blue Card). The facilitators and Queensland University of Technology research staff will follow the directions of supervising school staff regarding access to child participants and the location of testing. Testing will take place in an accessible area designated by the school principal or supervising teacher, in proximity to normal classroom activities. As required by the Health and Safety requirements for Queensland schools, the supervising teacher will be aware of the intervention testing circumstances. Assistance will be available from school staff when required. The facilitators and Queensland University of Technology research staff will follow the required procedures for visitors to the school.

The intervention will be delivered during three × one hour sessions over a three week period, and each session will address a different construct. Week one will be designed to encourage supportive sun protection related attitudes and beliefs. Week two will focus on fostering perceptions of friendship group normative support for sun protection. Week three will aim to increase perceptions of control/self-efficacy over using sun protection. Activities for the intervention will include group based discussions, practical sessions on being sun safe (e.g., role playing activities to convince friends to be sun smart), watching relevant sun safety DVDs, setting sun safe goals, and students creating their own internet and/or text message campaigns to encourage sun safety amongst young people. At the conclusion of each session, participants and facilitators will evaluate program content, materials, and delivery.

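### The 130 completers per group do not follow from the stated inputs (105 would do), and the stated 95% power is not assured because it makes no allowance for group delivery

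*Protocol article*

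**What the plan says.** The Sample size section of the protocol article lists its inputs: "Significance level (alpha) was established at 0.05", "power (1-beta) was set at 95" per cent, and "effect size was determined at .25". It describes the target as "A total sample of approximately 260 (400-140) completing participants (130/group"), "required to detect a medium effect in sun safety behaviour". On the source it says: "This sample size was determined by power analysis using the G*Power program". It concludes that "for a 95% chance of detecting as significant a 4 week difference in sun safe behaviour, approximately 130 participants in each group are needed". It names neither the effect-size metric nor the test, and it lists no intraclass correlation, cluster size or design effect.

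Elsewhere in the article:

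- Study design randomises adolescents 1:1.
- The Abstract and the Intervention section describe three one-hour sessions, led by a trained facilitator in class time. "Activities for the intervention will include group based discussions, practical sessions on being sun safe", with role play among the examples.
- Data Analyses plans general linear models for change outcomes with group, time and their interaction. No class or delivery-group term is mentioned.

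**The concern.** There are two separate problems with one sentence.

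First, the article presents 130 per group as the output of a power calculation. A reader who enters the listed inputs for a difference between two groups gets a different number, so it is unclear what was calculated.

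Second, students who share sessions, a facilitator and peer discussion are likely to have correlated outcomes. That correlation inflates the variance of the intervention-arm mean. A calculation for independent observations then overstates power.

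At stake is the 95% quoted for behaviour, one of the two primary outcomes. If the real figure is in the 80s or lower, a null result would be read as stronger evidence against a medium effect than it is.

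**Working it through.** **Inputs from the Sample size section.** Alpha 0.05 (taken as two-sided), power 0.95, effect .25 called medium, two equal groups, 35% attrition from 400.

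**Assumptions, not in the documents.** Delivery groups of 25 enrolled, so 25 × 0.65 ≈ 16 completers; ICC 0.02, 0.05 or 0.10; equal total variance in the two arms.

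**Step 1: the attrition figure.** 400 × 0.65 = 260, and 260 / 0.65 = 400. This step is correct.

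**Step 2: the power calculation.** A medium effect of .25 fits Cohen's f. For two equal groups d = 2f = 0.5.

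- Normal approximation: n per group = 2(1.960 + 1.645)² / 0.5² = 2 × 12.996 / 0.25 ≈ 104.
- Exact noncentral F, noncentrality N f² = 0.0625 N, with 1 and N − 2 df: N = 210 gives 95.0%, that is 105 per group. N = 260 gives 98.0%.

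Other standard set-ups with f = .25, for 95% power:

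| Test | Total N |
|---|---|
| 2 numerator df (e.g. three time points, noncentrality N f²) | 250–252 |
| 3 numerator df | 279–280 |
| Repeated measures, between-group, correlation 0.5, 2 or 3 times | 158 or 142 |
| Repeated measures, group by time, correlation 0.5, 2 or 3 times | 54 or 44 |
| Two groups, alpha halved for two primary outcomes | 246 |

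None gives 260. The nearest is the 2-df test, where N = 251 reaches 95% and 260 gives 95.7%.

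**Step 3: clustering in the intervention arm only.** This matches individual randomisation followed by group sessions. With m = 16, the design effect is DE = 1 + 15 × ICC in that arm and 1 in the control arm. In standard deviation units SE = √((DE + 1) / 130), and the standardised effect is 0.5 / SE.

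| ICC | DE | SE | 0.5 / SE | Power, large df | Power, 7 df |
|---|---|---|---|---|---|
| 0.02 | 1.30 | 0.133 | 3.76 | 96% | 89% |
| 0.05 | 1.75 | 0.145 | 3.44 | 93% | 84% |
| 0.10 | 2.50 | 0.164 | 3.05 | 86% | 74% |

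The large-df column is Φ(0.5/SE − 1.960). The last column uses the noncentral t with 7 df, because 130 / 16 ≈ 8 delivery groups. That is a cautious choice, since the unclustered control arm also contributes information.

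**Step 4: how much clustering the surplus absorbs.**

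- Both arms clustered: 260 / 210 = 1.24. At 25 completers per class, ICC = 0.238 / 24 ≈ 0.01.
- Intervention arm only: (DE + 1) / 2 = 1.238, so DE ≈ 1.48. At 25 per group, ICC = 0.476 / 24 ≈ 0.02; at 16 per group, 0.476 / 15 ≈ 0.03.

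**The case against.** **The number may have a sound origin.** The article says approximately, and the planned model has three time points, so its group-by-time term has 2 numerator df. A 2-df calculation gives 251, and 260 is 3.6% above it. The four-week difference could also mean change over four weeks. This is a plausible origin, but the article does not state it. A true repeated-measures calculation for that interaction gives much smaller totals. It is equally possible that 260 is simply 400 less 35%.

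**The discrepancy is in the safe direction.** This stands. Without clustering, 130 per group deliver more than the article claims.

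**Baseline information could recover power.** If the analysis adjusted for baseline with an assumed correlation of 0.5, the variance would fall by a factor of 1 − 0.5² = 0.75, and the large-df figures would rise to about 99%, 98% and 94%. But a plain change score at the same correlation has variance 2(1 − 0.5) = 1 and gains nothing. The article states no correlation and does not claim this gain.

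**A condensed article may leave the ICC to the full protocol.** This is fair as far as it goes, and the absence of an ICC alone would not be a finding. The point is that the article gives 95% as the result of listed inputs, and those inputs neither yield the number nor include a clustering term.

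**Stronger readings a reader might infer.** One is that .25 is Cohen's d, which would put power at 52%. The article calls the effect medium, which fits f = .25 and not d = .25, so the text does not support that reading. Another is that whole classes are allocated, which gives about 81% with 16 classes and ICC 0.05. Study design says adolescents are randomised, so that figure belongs to a design the article does not describe.

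**Conclusion.** The point holds in two limited parts. The stated 130 per group does not follow from the stated inputs for a two-group comparison: 105 suffice and 130 give 98.0%, an error on the conservative side. The stated 95% is not assured once group delivery is counted. With individual randomisation and clustering in the intervention arm only, it is about 96% / 93% / 86% at ICC 0.02 / 0.05 / 0.10, or about 89% / 84% / 74% with roughly 7 df. If both arms are clustered, the surplus over 210 is used up at a design effect of 1.24.

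It would go too far to say that 95% is not delivered. At ICC 0.02 with large df the target is met, and smaller groups or a lower ICC also leave it intact. The inconsistency with the listed inputs is firm, given f = .25 and a two-group test. The size of the clustering loss rests on the assumed ICC and group size.

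**What to change.** Keep n = 400 and rewrite the Sample size paragraph:

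1. Name the metric (Cohen's f = .25, equivalent to d = 0.5 for two groups) and the test, chosen to match the planned group-by-time model.
2. Reconcile 260 with those inputs, or say that 260 is what 400 recruits leave after 35% attrition and give the power that results.
3. State an assumed ICC and delivery-group size, with the reason for each.
4. Restate the power, or the effect detectable at 95% power, for the allocation actually used. For the two-group comparison at 130 per group, the detectable d is about 0.45 without clustering. With intervention-arm clustering at 16 per group it is 3.605 × SE ≈ 0.48, 0.52 and 0.59 at ICC 0.02, 0.05 and 0.10 (large df).

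Figures for class-level allocation should appear only if classes are in fact the unit allocated.

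The cost is one paragraph and no further participants. The quoted power may become less favourable, depending on the ICC and group size assumed.

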### Study Conditions

#### Control

Control participants will be wait-listed to receive the study intervention. At the completion of the study, participating schools will be offered the opportunity to have trained facilitators run the program sessions to control group participants.

#### Intervention

The intervention will focus on: (i) encouraging supportive sun protective attitudes and beliefs, (ii) fostering perceptions of normative support for sun protection behaviour, and (iii) increasing perceptions of control/self-efficacy over using sun protection. Intervention sessions will be facilitated by trained persons from the Cancer Council Queensland and Queensland University of Technology. Facilitators and Queensland University of Technology research staff will be authorised to deliver the intervention with secondary school students during school hours, and all study staff directly involved with the participants and the running of the intervention will be approved to work with minors (have a current Positive Notice Blue Card). The facilitators and Queensland University of Technology research staff will follow the directions of supervising school staff regarding access to child participants and the location of testing. Testing will take place in an accessible area designated by the school principal or supervising teacher, in proximity to normal classroom activities. As required by the Health and Safety requirements for Queensland schools, the supervising teacher will be aware of the intervention testing circumstances. Assistance will be available from school staff when required. The facilitators and Queensland University of Technology research staff will follow the required procedures for visitors to the school.

The intervention will be delivered during three × one hour sessions over a three week period, and each session will address a different construct. Week one will be designed to encourage supportive sun protection related attitudes and beliefs. Week two will focus on fostering perceptions of friendship group normative support for sun protection. Week three will aim to increase perceptions of control/self-efficacy over using sun protection. Activities for the intervention will include group based discussions, practical sessions on being sun safe (e.g., role playing activities to convince friends to be sun smart), watching relevant sun safety DVDs, setting sun safe goals, and students creating their own internet and/or text message campaigns to encourage sun safety amongst young people. At the conclusion of each session, participants and facilitators will evaluate program content, materials, and delivery.

### Study and Data Integrity

The study design will be guided by the CONSORT (Consolidated Standards of Reporting Trials) statement [31]. Randomisation will occur using a computer-generated random number sequence undertaken by the study manager and concealed from investigators. The intervention protocol will be detailed in a study manual, and a minimum of 20% of intervention sessions will be reviewed by an external reviewer to ensure adherence to the delivery of the intervention protocol. Self-report measures are commonly used to assess sun-exposure although they may be subject to bias [32], therefore a sub-sample (n = 40) of participants will wear polysulphone (sun) badges over a two day period to check the reliability of the self-reported sun exposure data.

### Measurement

Data will be collected by self-reported pre- and post-intervention questionnaires. The pre-intervention questionnaire will be completed in the class room one week before the commencement of the intervention. The post-intervention questionnaires will be completed at one week and four weeks after the commencement of the intervention.

#### Variables

Demographic data collected pre-intervention will include age (in years) and sex (male or female). Data will also be collected on colour of skin before tanning (very fair, fair, olive or brown, Asian, black), colour of skin with repeated exposure to the sun light without protection (go very brown and deeply tanned, get moderately tanned, get mildly or occasionally tanned, get no suntan at all or occasionally get freckled), natural hair colour (black, dark brown, light brown, dark blonde, light blonde, red), eye colour (dark brown, light brown, green, blue), and hours spent in the sun in the past week.

Primary outcome variables will assess the effectiveness of the intervention in improving students' sun protection intentions and behaviour. Secondary outcome variables will assess the effectiveness of the intervention as a means of improving students' attitudes toward performing sun protective behaviours (i.e., attitudes), perceptions of normative support to sun protect (i.e., subjective norms, group norms, and image norms), and perceived control over performing sun protective behaviours (i.e., perceived behavioural control) (Table 1).

**Table 1 T1:** Primary and Secondary Outcome Measures

Domain	Variable	Number of items	SCALE	MEASUREMENT STRATEGIES
**Primary outcome variables**				

	Intention	4	1 (strongly disagree) to 7 (strongly agree)	"I am willing to perform sun-protective behaviours."; "I intend to perform sun-protective behaviours."; "I plan to perform sun-protective behaviours."; "It is likely that I will perform sun-protective behaviours."

	Behaviour	3	1 (never) to 7 (always)	"Think about the past week. In general, how often did you perform sun-protective behaviour?" "Think about the past week, how often did you perform sun-protective behaviour on a school day?"; "Think about the past week, how often did you perform sun-protective behaviour on the weekend?"

**Secondary outcome variables**				

	Attitude	6	1 (pleasant) to 7 (unpleasant) 1 (good) to 7 (bad) 1 (wise to 7 (unwise) 1 (difficult) easy (7) 1 (nice) to 7 (awful) 1 (negative) to 7 (positive)	"Performing sun-protective behaviours every time I go in the sun for more than 10 minutes during the next week, would be..."

	Subjective Norms	2	1 (strongly disagree) to 7 (strongly agree)	"Those people who are important to me would want me to perform sun-protective behaviours." and "Most people who are important to me would approve of me performing sun-protective behaviours."

	Perceived Behavioural Control	4	1 (strongly disagree) to 7 (strongly agree)	"I have complete control over whether I perform sun-protective behaviours."; "It is mostly up to me whether I perform sun-protective behaviours."; "If I wanted to it would be easy for me to perform sun-protective behaviours."; "I am confident that I could perform sun-protective behaviours."

	Group Norms	4	1 (strongly disagree) to 7 (strongly agree) 1 (none) to 7 (all)	"Most of my friends perform sun-protective behaviours." and "My friends think that performing sun-protective behaviours is a good thing to do." "How many of your friends would think that performing sun-protective behaviours every time you are out in the sun for more than 10 minutes in the next week is a good thing to do?" and "How many of your friends would perform sun-protective behaviours every time they are out in the sun for more than 10 minutes during the next week?"

	Image Norms	5	1 (strongly disagree) to 7 (strongly agree)	"Young celebrities and movie stars always seem to have a tan."; "I see more examples of models who have pale skin on TV and in magazines than I used to."; "I think that to be a successful movie star or TV star you should have a tan."; "It seems that society wants young people to have a tan."; "I can think of many young movie stars and TV stars who have pale skin."

The target behaviour is "Performing sun-protective behaviours (i.e., using SPF 30+sunscreen, wearing protective clothing such as a hat, long-sleeved shirt and sunglasses, and seeking shade between 10 am and 3 pm) every time you go in the sun for more than 10 minutes during the next week". To maximise congruence between the prediction and criterion variables, the TPB variables (i.e., intention, attitude, subjective norms, perceived behavioural control) are measured at the same level of specificity in terms of action, target, and time [15]. The items are constructed in strict accordance with TPB recommendations [15] and are each scored on a 7-point Likert scale, except for attitude, which is scored on 7-point semantic-differential scales.

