The Theory of Planned Behaviour [TPB; 15] is a model developed in response to identified inconsistencies between people's attitudes and actions (see Figure 1). The TPB is a well-validated model that has been used to explicate the attitude-behaviour relationship and accounts for the complexity of people's decision making. It specifies intentions as the most proximal determinant of behaviour with intentions being influenced by attitude (positive or negative evaluations of performing a behaviour), subjective norm (perceived social pressure to perform or not perform a behaviour), and perceived behavioural control (perceived ease or difficulty of performing a behaviour; also thought to be a direct predictor of behaviour; [15]). Attitude, subjective norm, and perceived behavioural control are informed by underlying behavioural (i.e., costs and benefits), normative (i.e., specific referents' (dis)approval), and control beliefs (e.g., barriers and facilitators), respectively, and it is these beliefs that can be used to design interventions [16]. According to the theory, other factors relevant to sun protection decisions, such as sun safety knowledge or perceptions of risk for skin cancer/damage, are not believed to influence intentions or behaviour directly but would instead be expected to inform underlying sun protection beliefs [15].

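### The attitude score includes a difficult-easy pair, although the protocol defines perceived ease or difficulty as perceived behavioural control, which blurs two separate secondary outcomes

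*Protocol article*

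**What the plan says.** The Background section of the protocol article defines the two constructs separately. One is "attitude (positive or negative evaluations of performing a behaviour"; the other is "perceived behavioural control (perceived ease or difficulty of performing a behaviour; also thought to be a direct predictor of behaviour".

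Table 1 gives attitude six items. All six are semantic-differential pairs under one stem, "Performing sun-protective behaviours every time I go in the sun for more than 10 minutes during the next week, would be", and one pair is anchored "1 (difficult) easy (7". Perceived behavioural control has four agree-disagree items, one of which is "If I wanted to it would be easy for me to perform sun-protective behaviours".

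The Variables section lists attitude and control as separate secondary outcomes. The text after Table 1 states that the items follow the theory's recommendations strictly. In the Intervention section the first session is aimed at attitudes and beliefs, while "Week three will aim to increase perceptions of control/self-efficacy over using sun protection". The Data Analyses section provides a general linear model for each change outcome, with group, time and their interaction. The article does not say how items are combined into a scale score.

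**The concern.** A student who answers the difficult-easy pair rates how easy or hard the behaviour would be. By the article's own definition that is perceived control, not evaluation. Nothing in the article explains why the pair sits under attitude.

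The third session sets out to raise perceived control. If it makes sun protection feel easier, part of that change enters the attitude score even when students' evaluation of sun protection has not moved. Attitude has its own model, so the carry-over would be read as an attitude effect. What is at stake is the reading of which construct changed, and the Study Aim section names attitudes, normative support and self-efficacy as distinct routes to intention and behaviour.

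**Working it through.** **Is the pair really a counted attitude item?** Table 1 states 6 attitude items. The listed pairs are pleasant-unpleasant, good-bad, wise-unwise, difficult-easy, nice-awful and negative-positive, which makes 6. The control row states 4 items and lists 4. Both counts reproduce, so the pair belongs to the attitude scale as printed and is not a misplaced table cell. Without it, five evaluative pairs remain.

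**Definitions against items.**

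| Construct | Definition in Background | Items on ease in Table 1 |
|---|---|---|
| Attitude | positive or negative evaluation | 1 of 6 (difficult-easy pair) |
| Perceived behavioural control | ease or difficulty | 1 of 4 (would be easy, if wanted) |

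**Raw carry-over.** Assume an equally weighted mean with all pairs aligned in direction. Alignment is needed because four pairs run from positive to negative and two, including difficult-easy, run from negative to positive. The attitude shift is then the item shift divided by 6, if the other five pairs do not move:

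- 1 point: 1/6 = 0.17
- 2 points: 2/6 = 0.33
- 3 points: 3/6 = 0.50

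**Standardised carry-over.** Assume also equal item variances and a common inter-item correlation r. In units of the item SD, the SD of a six-item mean is √((1 + 5r)/6). An effect d on the difficult-easy pair alone gives

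attitude d = (d/6) / √((1 + 5r)/6).

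For d = 0.5:

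- r = 0.2: 0.0833 / √(2/6) = 0.0833 / 0.577 = 0.144
- r = 0.7: 0.0833 / √(4.5/6) = 0.0833 / 0.866 = 0.096

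**Chance of declaring an attitude effect.** This uses the 130 completers per arm from the Sample size section, a two-sided 5% level and a simple comparison of two means with independent participants. With D for the attitude d, the probability is Φ(D/√(2/130) − 1.96) + Φ(−D/√(2/130) − 1.96), where √(2/130) = 0.124.

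| Ease-only item d | Attitude d (r = 0.7 to 0.2) | Probability of significance |
|---|---|---|
| 0.25 | 0.05 to 0.07 | 7% to 9% |
| 0.5 | 0.10 to 0.14 | 12% to 21% |
| 1.0 | 0.19 to 0.29 | 34% to 64% |

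With no change in evaluation, the nominal figure is 5%.

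**After the change.** With the pair out of the attitude score, its weight there falls from 1/6 to 0, and so does the carry-over through it.

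The article gives no SDs, correlations or expected item effects. The values of r and d are therefore assumptions that show the range.

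**The case against.** Four arguments can be made for leaving the scale as it is.

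- **Difficulty can be seen as a cost of the behaviour.** The Background section says that costs and benefits inform attitude, and that risk-related factors can show up in both costs and control perceptions. This softens the conflict. But those remarks concern underlying beliefs, while the same section places ease or difficulty itself under control.
- **The two ease questions differ.** The attitude stem is unconditional and names a specific behaviour over the next week; the control item is conditional on wanting to. This stands. A reader might infer that one item is counted in two scores, or that the two outcomes are correlated by construction. Table 1 does not support that: the content overlaps, but no response enters both scores.
- **Attribution does not hinge on this pair.** This also stands. A reader might infer that the trial cannot tell an attitude change from a control change. Yet five of six attitude pairs and all four control items lie outside the dispute. Attribution to a particular session is limited mainly because the three sessions are delivered as one package against a wait-list. Nor was the pilot's unclear mechanism a matter of item overlap: the article puts it down to few participants with follow-up data and a short follow-up.
- **The scoring is not stated and may be set out in a fuller document.** That is fair, and its absence from an article is no fault. It makes the size of the carry-over conditional, but not the placement of the pair, which Table 1 fixes.

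**Conclusion.** The point holds as a modest flaw in how a secondary outcome is composed. Table 1 puts a rating of ease or difficulty into the attitude scale, against the article's own definition and its statement that items follow the theory strictly.

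Under an equally weighted, direction-aligned mean, a 1-point gain in ease alone adds about 0.17 point to attitude. An ease-only item effect of d = 0.5 adds about d = 0.10 to 0.14 for r between 0.2 and 0.7. An attitude effect near d = 0.2 or more from this source would need an ease-only effect of about d = 1.0, which is large. The scoring rule, the correlations and the item effects are all assumed; the overlap in content is read directly from the text.

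The consequence is confined to how attitude and control are read as separate secondary outcomes. Intention, behaviour and the sample size are unaffected.

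**What to change.** Before outcome data are seen, specify that attitude is scored from the five evaluative pairs (pleasant, good, wise, nice, positive), aligned in direction. Report the difficult-easy pair on its own. Adding it to the control scale is less attractive: two of five control items would then concern ease, and a semantic-differential rating would be mixed with agree-disagree ratings. Keep the six-item attitude score as a sensitivity analysis, so that readers can see whether the conclusion depends on the pair.

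The questionnaire stays as it is, and no new data or participants are needed. The cost is a shorter attitude scale and less direct comparability with the pilot if that study scored six items. Timing matters, because a rescoring after the results are known would look data-driven.
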